### Sample size

Power analysis performed in G*Power^
31
^ showed that 39 patients (total) would be needed to attain statistical
significance. Based on previously published data investigating a UK-based SEP
that adopted a similar exercise circuit^
32
^ and converting the interquartile range to standard deviation,^
33
^ a median change in MWD of 143 m and a pooled standard deviation of 111.3
m was calculated. A power of 90% and a significance level of 5% were assumed. A
drop-out of approximately 30% will be allowed, yielding a required sample size
of 51 patients (17 per group) to be randomised.

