**Objective::**

The objective of this study is to directly compare the effects of exercise
prescribed at three different levels of claudication pain on walking
performance.

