### Data analysis

The primary endpoint for the statistical analysis is the change in MWD from
baseline to 12 and 24 weeks. An analysis of covariance (ANCOVA) will be used to
compare MWD across three time points with baseline MWD as a covariate. Post hoc
analysis for the main effects and interactions will be assessed using a
Bonferroni adjustment. Group differences will be compared using simple main
effects. Secondary outcomes such as PFWD distance will be evaluated adopting the
same approaches. Qualitative data will be analysed using inductive thematic
analysis whereby themes are identified from the transcripts.^
35
^

Data will be entered into SPSS (IBM, New York, USA) by a single investigator who
will maintain the overall responsibility for data quality. The primary and
secondary outcome analyses will be conducted at the conventional (two-sided) 5%
alpha level. Where parametric data distribution allows, partial eta squared
values will also be reported. To reduce the risk of false-positive claims,
secondary analyses will be considered exploratory if non-significant results are
obtained from the primary analysis. All analyses will be performed on an
intention-to-treat basis. All data will be summarised and reported in accordance
with the Consolidated Standards of Reporting Trials (CONSORT) guideline, the
template for intervention description and replication (TIDieR) and recently
published recommendations.^36–38^

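### The sample size rests on a 143 m change reported for a supervised exercise programme, not on a stated difference between pain levels, so the 90% power is not tied to the trial's question

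*Protocol article*

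**What the plan says.** The Objective in the abstract sets a comparison between arms: "The objective of this study is to directly compare the effects of exercise" prescribed at three levels of claudication pain. Under Study procedures, every participant is randomised to a 24-week SEP. The arms differ in the pain level at which exercise stops, and no arm goes without exercise.

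The Sample size section reports that a G*Power analysis "showed that 39 patients (total) would be needed to attain statistical" significance. Its inputs are introduced with "Based on previously published data investigating a UK-based SEP" that used a similar circuit. After "converting the interquartile range to standard deviation", the section arrives at "a median change in MWD of 143 m and a pooled standard deviation of 111.3" m. It adds that "A power of 90% and a significance level of 5% were assumed" and that a "drop-out of approximately 30% will be allowed", giving 51 randomised (17 per group).

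The Data analysis section plans an ANCOVA on maximal walking distance (MWD) with baseline MWD as covariate, Bonferroni-adjusted post hoc comparisons and a two-sided 5% level.

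**The concern.** The planning effect is described as a change in MWD in a study of an SEP. Nothing in the section describes it as a difference between exercise prescribed at different pain levels. Since all arms receive an SEP, and the Introduction itself cites evidence that mild or pain-free exercise improves walking, some gain is to be expected in every arm. The quantity that decides the trial is the difference between those gains, and the section neither states nor justifies one.

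The Introduction motivates the trial by the shortage of adequately powered comparisons of pain levels. A reader will take the 90% as power for that comparison. If it applies only to a very large contrast, the trial's ability to answer its question is overstated, and a non-significant result would be easy to over-read.

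**Working it through.** **Inputs.** Effect 143 m, SD 111.3 m, power 90%, 39 analysed and 51 randomised (Sample size); two-sided 5% (Data analysis); three equal arms. Standardised effect d = 143 / 111.3 = 1.285.

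**1. Reproducing 39.** The section does not name the test, so several were tried.

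- *Two arms, normal approximation.* n = 2 × (1.960 + 1.282)² × (111.3/143)² = 12.73, so 13 per arm and 13 × 3 = 39.
- *Three-group F test, one arm 143 m from two equal arms.* SD of the means = 143 × √2/3 = 67.4 m; f = 67.4/111.3 = 0.606. The noncentral F (noncentrality N × f²) needs N = 38, or 39 in equal arms, with power 91%.
- *Three-group F test, equally spaced arms (0, 71.5, 143).* f = 1.285/√6 = 0.525. Power at 39 is 81%, and 51 would be needed.
- *The same equally spaced arms, averaging two measurements with an assumed correlation of 0.5.* The variance factor is (1 + 0.5)/2 = 0.75, so f = 0.525/√0.75 = 0.606, which again gives 39.
- *Within-arm change, paired t test.* 9 per arm (power 92%), 27 in total. This does not match.

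Every route found to 39 uses 143 m as a difference between arms. They disagree on where the third arm lies.

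**2. Detectable difference with 39 analysed, residual SD 111.3 m.** With one covariate, 90% power needs f = 0.595.

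- One arm differs from both others: 0.595 × 111.3 × 3/√2 = 140.5, about 141 m.
- Equally spaced arms: 0.595 × 111.3 × √6 = about 162 m from lowest to highest.

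**3. Power at smaller differences.** The documents give no expected difference between pain levels, so these are assumptions (71.5 m is half of 143 m). Overall F test, 39 analysed, residual SD 111.3 m:

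| Largest difference | One arm differs | Equally spaced |
|---|---|---|
| 143 m | 91% | 81% |
| 100 m | 62% | 49% |
| 71.5 m | 35% | 27% |
| 50 m | 19% | 15% |

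With all 51 analysed, 71.5 m gives 45% or 35%.

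**4. Allowing for the baseline covariate.** The section does not make clear whether 111.3 m is the SD of the change or of MWD itself. If it is the SD of MWD, the residual SD is 111.3 × √(1 − r²). For assumed r, at 71.5 m with one arm differing:

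| r | Residual SD | N = 39 | N = 51 |
|---|---|---|---|
| 0.5 | 96.4 m | 45% | 57% |
| 0.7 | 79.5 m | 62% | 75% |
| 0.8 | 66.8 m | 78% | 89% |

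At r = 0.7 the difference detectable with 90% power at N = 39 is 0.595 × 79.5 × 3/√2, about 100 m.

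**5. Precision of a pairwise difference.** With 13 per arm, residual SD 111.3 m and 36 error degrees of freedom, the unadjusted 95% CI half-width is 2.028 × 111.3 × √(2/13), about 89 m.

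**The case against.** Several stronger readings are tempting, and the document does not support them.

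- *The plan assumes that one pain level beats both others by 143 m.* That pattern reproduces 39, but so does a two-arm approximation that says nothing about the third arm, and so does an equally spaced pattern with repeated measurements. The pattern of means is unknown.
- *143 m is a before-to-after gain.* The section says only that it is a median change with a pooled SD. Pooling could be over time points or over groups, and the source is not at hand. What can be said is that it is not described as a contrast between pain levels. If it were SEP versus control, it would still not be this trial's contrast.
- *A non-significant result is the likely outcome.* That needs the true difference between pain levels, which the document does not give. The Introduction calls the optimal level unclear and only cautiously expects maximal pain to do best.
- *The authors would read a null result as equivalence, or would lead with partial eta squared.* The plan says neither. Partial eta squared is reported in addition, and group comparisons with Bonferroni adjustment are already planned.

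The best substantive defence is the baseline covariate: power figures using the full 111.3 m may be too pessimistic. That stands, and is why a range is shown. It helps only as far as 111.3 m does not already describe change. Even at an assumed correlation of 0.8 with all 51 analysed, power at 71.5 m with one arm differing is 89%; at lower correlations or with fewer analysed it is well below 90%.

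Nor is this a detail that an article simply leaves to a fuller document. The section does state an effect, but not one for the comparison being made.

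**Conclusion.** The point holds. The only effect in the sample size calculation comes from published data on an SEP and is not described as a difference between pain levels, although the trial compares three arms that all receive the SEP. Taking 111.3 m as the residual SD, the stated 90% holds only if pain levels differ by about as much as the whole change reported for an SEP: about 141 m if one arm differs, about 162 m in all if the arms are equally spaced. Half of 143 m has 35% or 27% power with 39 analysed.

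This rests on three things: the inference, from reproducing 39, that 143 m was entered as a between-arm contrast; the smaller differences, which are assumed; and the meaning of 111.3 m. If that is the SD of MWD, assumed correlations of 0.5 to 0.8 put power at 71.5 m (one arm differing) at 45% to 78% for 39 analysed and 57% to 89% for 51. The size of the shortfall is therefore uncertain. The absence of a stated and justified between-arm target is not.

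**What to change.** Keep 51 randomised and rewrite the Sample size paragraph to:

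1. say what 143 m is (change or contrast, and in which groups) and whether 111.3 m is the SD of change or of MWD;
2. state and justify the target difference in MWD change between pain levels;
3. name the test and the assumed pattern of the three means;
4. replace the unqualified 90% with the between-arm difference detectable at that power, and give power at smaller differences (for example 50, 70 and 100 m) over a range of baseline correlations.

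In the Data analysis section, add that pairwise differences in MWD change will be reported with 95% CIs, and that a non-significant result will not be read as equivalence of pain levels.

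The cost is wording only. The stated power becomes less favourable.

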### Randomisation and blinding

The random allocation sequence will be generated by the trial statistician on a
1:1 basis using a computer program random number generator. To ensure allocation
concealment, researchers will request randomisation from the principal
investigator on completion of all baseline assessments using a sealed, opaque,
sequentially numbered envelope. All outcome assessors will be blinded as will
the trial statistician. Exercise professionals delivering the interventions
cannot be blinded; however, they will not be involved in data analysis or
reporting.

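### Randomising 51 patients does not cover the stated 30% drop-out: it leaves about 36 completers, not the 39 required, and covers only 23.5%

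*Protocol article*

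**What the plan says.** All the figures are in the Sample size section of the protocol article. The G*Power calculation "showed that 39 patients (total) would be needed". Its inputs are "a median change in MWD of 143 m and a pooled standard deviation of 111.3" m, and "A power of 90% and a significance level of 5% were assumed". The allowance for losses follows directly: "drop-out of approximately 30% will be allowed, yielding a required sample size" "of 51 patients (17 per group) to be randomised". No inflation formula is printed, and no other drop-out rate or denominator is given. The Abstract repeats 51 as the result of the power calculation.

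**The concern.** The section makes three statements: 39 evaluable patients are needed, about 30% may drop out, and 51 will be randomised. Drop-out is ordinarily a share of those who enter the trial, so the number randomised must be the number needed divided by the share retained. The printed 51 looks instead like the number needed plus 30% of itself, which always gives too few.

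Two things are at stake. A reader is told that the trial keeps 90% power under the sponsor's own planning case for losses, and on its own figures it does not. Monitoring would also be misled: 30% of 51 is about 15 patients, so 15 losses would look within plan although 39 is already missed at the 13th. Substantial loss is plausible here. The Introduction says that completion is lower when exercise is prescribed at higher pain, and the Intervention section lets participants who cannot or will not reach the prescribed pain leave the study protocol.

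**Working it through.** **Inputs** (Sample size section unless noted)

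- Required number: 39 in total, 13 per group
- Drop-out: approximately 30%
- Number randomised: 51, 17 per group
- Power 90%, significance level 5%; the Data analysis section makes the tests two-sided
- Change 143 m, standard deviation 111.3 m, so d = 143/111.3 = 1.285

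**1. The base figure of 39.** The usual two-group normal formula gives n = 2(1.960 + 1.282)²/1.285² = 12.7, so 13 per group and 3 × 13 = 39. A three-group F test with one group differing from the other two by 143 m has f = 1.285 × √2/3 = 0.606. It needs 38, which is 39 in equal groups. The 39 is therefore reproducible and is taken as given.

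**2. The printed 51.**

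- Required number × (1 + drop-out) = 39 × 1.30 = 50.7, rounded up to 51. This matches and divides into 17 per group.
- Required number ÷ (1 − drop-out) = 39/0.70 = 55.7, rounded up to 56, or 57 (19 per group) for equal groups. This does not match.

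The article does not show the multiplication. It is inferred because it returns 51 exactly and the division does not. The next step does not depend on that inference.

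**3. What 51 delivers.**

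- Completers at 30% drop-out: 51 × 0.70 = 35.7, about 36. Per group, 17 × 0.70 = 11.9 against the 13 needed.
- Largest drop-out that still leaves 39: 1 − 39/51 = 12/51 = 23.5%.
- Shortfall in patients randomised: 56 − 51 = 5, or 57 − 51 = 6 with equal groups.

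**4. Does the word approximately cover the gap?** At 25% drop-out the requirement is 39/0.75 = 52, already more than 51. A rate of 23.5% is not a rounding of 30%.

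**5. Effect on power.** Three-group F test, two numerator degrees of freedom, 5% level, noncentrality N × f². The article does not give the pattern of group means, so two values of f are shown.

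| Assumption | N = 39 | N = 36 | N = 35 |
|---|---|---|---|
| f = 0.594, set so that 39 gives exactly 90% | 90.0% | 87.1% | 86.0% |
| f = 0.606, one group differing by 143 m | 91.1% | 88.4% | 87.4% |

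At the stated drop-out the cost is about 3 to 4 percentage points of power.

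**The case against.** Four points can be made for the plan as written.

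- **Denominator.** Adding 12 to 39 is an allowance of 12/39 = 30.8% of the required number, so the sentence is coherent if 30% is read as an add-on. But the article calls the 30% drop-out, which a reader takes as a share of those randomised, and no other denominator is stated. The point shows how the figure probably arose; it does not make it right.
- **Drop-out need not mean missing data.** The Outcome assessments section records withdrawal from the exercise programme, the Intervention section lets non-compliers continue in usual care, and analysis is by intention to treat. Some who stop may still be measured, so 36 is the low end for the number analysed. That stands as a limit on the harm. The Sample size section nevertheless treats drop-outs as lost when it inflates for them, and intention to treat does not supply treadmill distances that were not measured.
- **Covariate adjustment.** The analysis of covariance uses baseline walking distance. If, as an assumption, baseline explained 5%, 10% or 15% of the residual variance, power at 36 with f = 0.594 and one degree of freedom spent would be about 89%, 90% or 92%. So 90% power at 36 completers is possible. The article gives no such correlation and takes no credit for one, so the gain cannot be relied on to support the printed figure.
- **Size.** The loss is a few points of power, and the 143 m and 111.3 m inputs, a median and a converted interquartile range, are themselves uncertain. This is fair, and the point should not be presented as a threat to the trial. It is still a plain error in a published figure.

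**Conclusion.** The concern holds. The article's 39, 30% and 51 cannot all be true. At 30% drop-out, 51 patients leave about 36; 51 protects 39 completers only up to 23.5%. This rests on the printed figures and the ordinary meaning of drop-out, with each drop-out counted as lost to the analysis, as the allowance itself implies. That 51 came from multiplying by 1.3 is a strong inference, not something the article states.

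The power consequence is modest: 86% to 88% at 35 or 36 completers where 90% is claimed, for an unadjusted three-group F test and the two values of f shown. Other patterns of group means would give other figures.

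**What to change.** Keep 51 and correct the sentence in one of two ways.

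- **Preferred:** state that randomising 51 patients (17 per group) allows for 23.5% drop-out, that is, 39 of 51 completing. This needs no assumption about the group means.
- **Alternative:** keep 30% and state that about 36 patients would then complete, with power of about 87%. Name the test and the effect size behind that figure, because the article does not give them.

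The cost is one corrected sentence and a slightly less favourable stated figure. Recruitment, conduct and analysis do not change. If the sponsor wants both 90% power and a 30% allowance on these assumptions, the number randomised is 56, or 57 with equal groups: 5 or 6 more patients.

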### Data collection and management

The protocol and subsequent trial will adhere to the Standard Protocol Items:
Recommendations for Clinical Trials (SPIRIT) and adopt the SPIRIT checklist.^
34
^ Trial data will be collected on a case report form by the research team
at baseline, 12 and 24 weeks. The anonymised data will be stored using a
password-protected file on the University of Central Lancashire staff OneDrive
system and processed using an institutional Microsoft Surface Pro. All
electronic data will be anonymised and identifiable via a number only. Paper
data, that is, consent forms, will be kept in a locked filing cabinet in the
principal investigator’s office for a duration of 5 years after study
completion.

### Data analysis

The primary endpoint for the statistical analysis is the change in MWD from
baseline to 12 and 24 weeks. An analysis of covariance (ANCOVA) will be used to
compare MWD across three time points with baseline MWD as a covariate. Post hoc
analysis for the main effects and interactions will be assessed using a
Bonferroni adjustment. Group differences will be compared using simple main
effects. Secondary outcomes such as PFWD distance will be evaluated adopting the
same approaches. Qualitative data will be analysed using inductive thematic
analysis whereby themes are identified from the transcripts.^
35
^

Data will be entered into SPSS (IBM, New York, USA) by a single investigator who
will maintain the overall responsibility for data quality. The primary and
secondary outcome analyses will be conducted at the conventional (two-sided) 5%
alpha level. Where parametric data distribution allows, partial eta squared
values will also be reported. To reduce the risk of false-positive claims,
secondary analyses will be considered exploratory if non-significant results are
obtained from the primary analysis. All analyses will be performed on an
intention-to-treat basis. All data will be summarised and reported in accordance
with the Consolidated Standards of Reporting Trials (CONSORT) guideline, the
template for intervention description and replication (TIDieR) and recently
published recommendations.^36–38^

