## Introduction

Peripheral artery disease (PAD) is characterised by atherosclerotic lesions of the
arteries in the lower limbs, resulting in a reduction in blood flow.^
1
^ Globally, it is estimated that 236 million people are living with PAD, with
the number of cases increasing.^
2
^ A classic symptom of PAD is intermittent claudication (IC), characterised by
ischemic muscle pain in the leg precipitated by exertion and relieved by
rest.^3,4^ PAD is
associated with various comorbidities such as diabetes mellitus, hypertension and
dyslipidaemia, as well as reductions in physical function, quality of life and
balance.^3,5,6^ National and
international guidelines^4,7^
recommend exercise therapy as the first-line treatment for patients with IC,
generally advocating 2 h per week of a supervised exercise over a 3-month period,
with patients being encouraged to exercise to the point of moderate or maximal pain.
Exercise therapy, via supervised exercise programmes (SEPs), is supported by
high-quality evidence for its clinical and cost-effectiveness, costing less than a
tenth of angioplasty.^8,9^

Despite the plethora of evidence demonstrating the benefits of SEPs, less than half
of the vascular units in the United Kingdom have access to one and patient uptake
rates are low.^10,11^ One of the primary reasons for poor adherence may be the level
of pain prescribed during SEPs. Indeed, exercise-induced pain is a major barrier to
physical activity in this population,^
12
^ and the level of pain prescribed during SEPs influences completion rates.^
13
^ When exercise is prescribed at higher levels of pain, completion rates are
lower. However, current evidence and guidelines advocate exercising at moderate to
maximal pain,^7,14–16^ despite evidence to the
contrary, suggesting that mild- or pain-free exercise improves walking
ability.^17–20^ The lack of adequately
powered, randomised clinical trials investigating the effects of exercise prescribed
at differing levels of claudication pain has also been highlighted in a recent
scientific statement from the American Heart Association.^
16
^ As such, it remains unclear which level of claudication is optimal for
improving walking performance in patients with IC.^
21
^ The aim of this trial is to directly compare the effects of exercise
prescribed at different levels of claudication [pain-free (PF), moderate pain
(MOD-P) and maximal pain (MAX-P)] on (1) maximal and pain-free walking distance; (2)

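### If the primary ANCOVA is fitted as a classical repeated-measures model, a patient who misses the week-24 test also loses a valid 12-week MWD; a mixed model would keep it

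*Protocol article*

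**What the plan says.** The Data analysis section of the protocol article names two changes, from baseline to 12 weeks and to 24 weeks, as the primary endpoint. It gives one model for them: "An analysis of covariance (ANCOVA) will be used to compare MWD across three time points with baseline MWD as a covariate". The follow-up tests are described as a post hoc "analysis for the main effects and interactions will be assessed using a" Bonferroni adjustment, and groups are then compared by simple main effects. Partial eta squared is to be reported and the software is SPSS. The same section states: "All analyses will be performed on an intention-to-treat basis".

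Three other places bear on missing visits:
- Sample size: "A drop-out of approximately 30% will be allowed". No split by visit is given.
- Intervention: patients who cannot or will not reach the assigned pain level may leave and continue with usual-care exercise.
- Introduction: "When exercise is prescribed at higher levels of pain, completion rates are lower".

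The article does not use the terms repeated measures, complete case, listwise deletion, imputation or mixed model.

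**The concern.** An interaction needs a second factor, and the only factors described are group and time. The text therefore points to a single group-by-time model. With SPSS and partial eta squared, the usual way to fit it is the repeated-measures general linear model. That procedure works on one row per patient and excludes any row with a missing visit.

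A patient with a valid 12-week MWD and no 24-week MWD would then be removed from both comparisons. The 12-week result would describe only those who later attended week 24, a set chosen by an event after randomisation. The Methods give the 12-week assessment a purpose of its own, which is to make the findings applicable to UK programmes, and those are shorter than this one. That result should not depend on who is still being assessed at week 24. Precision is lost and, because the protocol expects completion to vary with prescribed pain, a comparison between arms could also be biased.

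**Working it through.** **Inputs from the Sample size section:** change in MWD 143 m, SD 111.3 m, power 90%, two-sided 5%, 39 evaluable patients, about 30% drop-out, 51 randomised.

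**The plan's own figures.** Two-group normal formula: n per group = 2 × (1.960 + 1.282)² × (111.3/143)² = 12.7, rounded up to 13; 3 × 13 = 39. The 51 is 39 × 1.3 = 50.7, rounded up. Both figures reproduce.

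**Patients with all visits.** 51 × 0.70 = 35.7, about 36.

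**12-week values discarded.** The share of losses falling between weeks 12 and 24 is an assumption. Total loss is 51 × 0.30 = 15.3.

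| Share of loss after week 12 | 12-week values available | Discarded by complete-case fit |
|---|---|---|
| 25% | 39.5 | about 4 |
| 50% | 43.4 | about 8 |
| 75% | 47.2 | about 11 |
| 100% | 51 | about 15 |

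With the 50% row taken as 43 and completers as 36, the loss is 7; unrounded it is 7.65. Hence 7 to 8.

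**Standard error at week 12.** It scales with 1/√n. Half of losses late: √(43/36) = 1.09, a rise of 9%. All losses late: √(51/36) = 1.19, a rise of 19%. A simulation with 17 per group, random loss and a baseline-to-12-week correlation of 0.5 (assumption) gave rises of 6%, 11% and 16% for 25%, 50% and 75% late. These are slightly higher because small, uneven groups cost a little more.

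**Power at week 12.** Three-group ANCOVA with one covariate, noncentral F. The protocol does not give the pattern of the three means, so assume one arm differs from the other two by 143 m: f = (143/111.3) × √2/3 = 0.606. Power is 88% with 36 patients and 94% with 43. With the middle arm halfway (f = 0.525) it is 77% against 85%.

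**Possible bias at week 12.** Assume 12-week change is normal with SD 111.3 m and that the log-odds of loss after week 12 fall by 0.5, 1 or 2 per SD of change. The completers' mean in an arm then shifts upward by:

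| Late loss in the arm | Slope 0.5 | Slope 1 | Slope 2 |
|---|---|---|---|
| 10% | 5.4 m | 10.1 m | 15.9 m |
| 15% | 8.1 m | 14.8 m | 22.6 m |
| 20% | 10.7 m | 19.3 m | 29.1 m |
| 30% | 15.9 m | 28.1 m | 41.7 m |

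The trial compares arms, so the difference between two shifts is what counts. With the same mechanism in both arms and late loss of 20% against 10%, the contrast shifts by 10.7 − 5.4 = 5.3 m, 19.3 − 10.1 = 9.2 m or 29.1 − 15.9 = 13.2 m. The standard error of a contrast with 12 per arm is 111.3 × √(2/12) = 45.4 m, so the shift is about 0.1 to 0.3 standard errors. The full one-arm figures apply only if late loss is confined to one arm.

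**The case against.** The deletion rule is inferred. The article says only ANCOVA. The same analysis could be run in SPSS MIXED or after imputation, and an ANCOVA at each visit would keep every 12-week value. Missing-data rules are commonly left to an analysis plan that is not shown, and the intention-to-treat sentence is the only statement about who is analysed. This stands as a limit, and the point is conditional for that reason. It does not remove the point. Separate ANCOVAs have no time effect and no group-by-time interaction, so they do not match the text, and partial eta squared belongs to the general linear model. The article has named its primary model, and the natural way to fit it sits badly with the stated principle.

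Stopping exercise is not the same as missing the test. The Outcome assessments section speaks of drop-out from the exercise programme, and a patient who stops but attends week 24 loses nothing under any model. This stands in full.

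A reader might infer that the plan breaches intention to treat outright, or that deletion will inflate the maximal-pain arm, which the investigators cautiously expect to do best. The documents support neither. No deletion is written. The Introduction links completion to prescribed pain, not to poor response, so the direction of any bias is conjecture.

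Some loss of precision was also budgeted, since the trial is sized on 39 evaluable patients. That completers number 36, not 39, comes from multiplying by 1.3 where dividing by 0.7 gives 56. That is a separate matter.

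**Conclusion.** The point holds conditionally, as a cheap improvement. If the model is a classical repeated-measures ANCOVA without imputation, each patient who misses only the week-24 test takes a valid 12-week MWD out of the analysis, and the 12-week comparison becomes one among completers.

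Under 30% loss of assessments, half of it after week 12, the cost at week 12 is 7 to 8 values, about 9% on the standard error, and about 88% power where 94% was attainable. These figures rest on an assumed split of drop-out by visit, on drop-out meaning missed tests, and on one arm differing by the planned 143 m.

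Bias in a between-arm contrast is possible but not established in size or direction. It is about 5 to 13 m in the scenario of 20% against 10% late loss with a common, assumed outcome-dependent mechanism, and larger only if loss is concentrated in one arm.

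**What to change.** In the Data analysis section, replace the ANCOVA sentence with a mixed model for repeated measures (SPSS MIXED):
- outcomes: MWD at 12 and 24 weeks;
- terms: arm, visit, arm-by-visit and baseline MWD;
- covariance: unstructured;
- patients: every randomised patient with at least one post-baseline MWD;
- report: the arm contrasts at each visit.

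This keeps every observed 12-week value, so loss after week 12 no longer selects who enters the 12-week comparison. The 24-week contrast then relies on missing values being explained by the observed data.

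The cost is one sentence, with the same software and the same data. The small downside is that partial eta squared gives way to adjusted mean differences with confidence intervals.

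### The 90% power holds only at an unadjusted 5%; the Bonferroni-adjusted arm comparisons have about 77% at the plan's own inputs, and a closed three-arm test would recover part of the loss.

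*Protocol article*

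**What the plan says.** The objective, in the Abstract, is a direct comparison of exercise "prescribed at three different levels of claudication pain on walking" performance.

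The Sample size section reports that a G*Power analysis "showed that 39 patients (total) would be needed to attain statistical" significance. Its inputs are "a median change in MWD of 143 m and a pooled standard deviation of 111.3" m, and it adds that "A power of 90% and a significance level of 5% were assumed". It names no test, no contrast between arms and no multiplicity adjustment. A loss of about 30% is then allowed for, which gives 51 randomised, 17 per group.

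The Data analysis section specifies ANCOVA with baseline MWD as covariate at a two-sided 5% level. It assigns the follow-up comparisons to a "Bonferroni adjustment. Group differences will be compared using simple main" effects. It does not say how many comparisons the adjustment covers.

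**The concern.** An overall three-group test shows that the pain levels are not all alike, not which level is better. The latter is what the objective asks, and the plan answers it with adjusted comparisons between arms. If the 90% was calculated for something else, a reader may take it as the chance of showing which pain level is better when that chance is lower. A pair that misses significance is then harder to interpret, because the protocol does not show how likely such a miss was.

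The second part concerns the choice of adjustment. With exactly three arms there is a procedure that controls the familywise error at the same 5% within a visit and loses less power than Bonferroni.

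**Working it through.** **Inputs.** From Sample size: 143 m, SD 111.3 m, 90% power, 5% level, 39 evaluable, 51 randomised, about 30% loss. From Data analysis: two-sided test, Bonferroni. Assumptions of this check: 143 m is a between-arm difference; three pairs are compared per visit, so each is tested at 0.05/3 = 0.0167; the SD is used without covariate gain unless stated.

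Standardised difference: d = 143/111.3 = 1.285.

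**Step 1: reproduce the 39.**
- Two-group normal approximation at 5%: n = 2(1.960 + 1.282)²/1.285² = 12.7, so 13 per arm and 3 × 13 = 39. Power at 13 is 90.6%. The exact two-group t test gives 88% at 13, or 89% with the variance pooled over three arms.
- Overall F test, one arm 143 m from two equal arms: f = 1.285 × √2/3 = 0.606. With N = 39 the noncentrality is 39 × 0.606² = 14.3 on 2 and 36 df, and power is 91.1%. With N = 36 it is 88.4%.

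Both routes give 39, and both use an unadjusted 5%.

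**Step 2: power of a Bonferroni comparison.** Noncentral t, with noncentrality d√(n/2) and error df 3n − 3. At n = 13 the noncentrality is 1.285 × √6.5 = 3.28 against a critical value of 2.51. The 12 per arm comes from 51 × 0.7 = 35.7, about 36 patients.

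| Analysed per arm | Power for a pair differing by 143 m |
|---|---|
| 12 | 73% |
| 13 | 77% |
| 17 (all 51) | 89% |
| 18 | 91% |

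Without covariate gain, the difference detectable with 90% power is about 167 m at 13 per arm and 175 m at 12. If the adjustment covered six comparisons (three pairs at two visits), power at 13 per arm would be about 68%.

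**Step 3: effect of the baseline covariate.** If 111.3 m is the SD of change and the variances at baseline and follow-up are equal, the ANCOVA residual SD is 111.3 × √((1 + ρ)/2), where ρ is the baseline/follow-up correlation. The protocol gives no ρ. For ρ = 0.5 the SD is 96.4 m and power at 13 per arm is 89%. For ρ = 0.9 it is 108.5 m and 80%.

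**Step 4: the closed procedure.** Test the overall group effect at 5%, and test each pair at 5% only if it is significant. If all three arms are equal, the overall test guards the error. If one arm differs from two equal arms, only one pairwise null is true, and it is tested at 5%. So the familywise error stays at 5% within a visit. Simulation gives 5.0% with all arms equal (Bonferroni uses 4.3%) and 5.0% for the remaining null pair when one arm is far away.

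Power at 13 per arm, by simulation:

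| Pattern of means | Comparison | Bonferroni | Closed |
|---|---|---|---|
| One arm 143 m from two equal arms | each true difference | 77% | 86% |
| | both true differences | 66% | 81% |
| Equally spaced over 143 m | extreme pair (143 m) | 77% | 80% |
| | each adjacent pair (71.5 m) | 21% | 35% |

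At 12 per arm with one arm apart, each true difference goes from 73% to 83% and both from 60% to 77%. With equal spacing the extreme pair goes from 73% to 77%.

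**The case against.** Six points weigh against this.

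- **The meaning of 143 m.** The protocol presents it as a median change taken from a published programme, not as a difference between arms. Every power above depends on the between-arm reading. This stands as a condition on all the figures. If the true differences are smaller, every power falls.
- **The source of the 39.** A reader might infer that it can only be the overall F test. The protocol names no test, and an unadjusted two-group calculation also gives 39. What stands is that neither route includes the adjustment.
- **The covariate and the losses.** 77% is not a fixed property of the trial. Step 3 gives 80% to 89%, and all 51 analysed gives 89% even without covariate gain. If 111.3 m were instead the SD of MWD itself, which the wording does not rule out, correlations of 0.5 to 0.7 would give 89% to 98%. This stands, so the power must be reported with its assumptions.
- **At least one difference.** With one arm apart, the chance that Bonferroni finds at least one of the two true differences is 89% at 13 per arm. The shortfall concerns a given pair, or both.
- **Bonferroni is legitimate.** It is valid and familiar, and it comes with simultaneous intervals. A reader might infer an error in the analysis; there is none.
- **Two visits.** The primary outcome is taken at 12 and 24 weeks. Running the closed procedure at both, with all arms equal, gives a simulated familywise error of about 7% to 9% (between-visit correlation 0.9 to 0.5). The 5% claim therefore holds within one visit only, and an adjustment across visits would lower the gains shown.

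**Conclusion.** The stated 90% and the planned arm comparisons do not refer to the same test. On the plan's own 143 m and 111.3 m, read as a between-arm difference and its SD, with three comparisons per visit and no covariate gain, a Bonferroni comparison of a pair that truly differs by 143 m has about 77% power at the 39 patients the calculation calls for, and 73% at the roughly 36 that a 30% loss would leave.

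The closed procedure did better than Bonferroni in both patterns examined. The gain for a 143 m pair is 9 points if one arm stands apart and about 3 if the means are equally spaced, and 90% is not reached in either pattern.

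A reader might go further and conclude that the trial has a one in four chance of missing any 143 m difference, or that non-significant pairs will be reported as equivalent. The documents support neither. The first treats one set of assumptions as fact, and nothing in the protocol plans an equivalence reading.

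**What to change.** 1. In Sample size, state which test and which pattern of means the 90% refers to. Add the power of the adjusted pairwise comparisons, or the detectable difference (about 167 to 175 m without covariate gain), with the assumptions behind it: 143 m as a between-arm difference, the number of comparisons, the number analysed, and any assumed baseline correlation.
2. In Data analysis, for the three arm comparisons at a given visit, replace Bonferroni by the closed procedure: a baseline-adjusted overall group test at 5%, then each pair at 5% only if that test is significant.
3. Handle error control across the 12- and 24-week visits separately, for example by naming one primary visit.

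The cost is wording only, with no extra patients. The stated power becomes less favourable, and the pairwise confidence intervals are no longer simultaneous and should be labelled so. If simultaneous intervals matter more to the sponsor, Bonferroni can stay, but the first change is still needed.
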